### Discontinuation

Participants will be withdrawn from the study if they withdraw informed consent or if they leave HAT. If a patient withdraws, only anonymised data gathered until this time point will be used. There will be no final examinations related to the study. Dropouts will be recorded as this relates to primary outcome (retention in treatment), but not followed up. Reasons for dropout will be assessed as this concerns acceptability of treatment. If a patient no longer receives IN DAM but remains in DAM treatment and does not withdraw informed consent, the scheduled visits will be conducted as planned.

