Currently available routes of DAM administration (IV and oral) are also increasingly insufficient due to changing patterns of substance use. In Switzerland and the EU, intranasal use is increasing, while inhalation and injection are decreasing [13, 14]. Given the current treatment options, individuals who are using opioids intranasally and entering HAT are prescribed oral DAM. A prescription of injectable DAM for non-injecting patients would ethically be unacceptable due to the higher risks associated with this route of administration. However, as previously mentioned, oral DAM has a much slower onset and less subjective effects. Hence, it often has limited efficiency in this patient group and may lead to treatment drop-out, ongoing illicit substance use, diversion of DAM tablets and delinquency. Some patients that would otherwise qualify for HAT and mainly use illicit opioids intranasally may even be discouraged from entering HAT for these aforementioned reasons [4].

In order to address these clinical gaps, minimise harm, and improve treatment outcomes, a novel route of DAM administration (intranasal; IN) has been developed as an alternative to IV or oral DAM for patients in HAT. It has a similar onset of effect as IM administration and is thus likely to produce the desired “rush” [15–17]. Currently prescribed off-label in a small number of HAT patients, it seems to be associated with less adverse effects than IV, IM or SC injection and has been suggested as a harm reduction measure to reduce HCV infection rates [18, 19]. Intranasal HAT (n-HAT) was first described in a case-series and was suggested as an important risk-reduced rapid-onset alternative to other forms of HAT [20]. In a recently published case-report, IN DAM administration improved treatment adherence and health outcomes in a patient who craved the fast onset of effect of DAM but was unable to inject intravenously [19]. Similarly, patients in HAT comparing a one-off administration of IN DAM with IV DAM reported advantages for IN administration such as ease and convenience of use, avoidance of needle hazards, and reduced stigma [15]. Finally, overdose from nasal use occurs much less often than from IV use [21].

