### Study procedures

Participants will be recruited only after the decision for nasal DAM is made by the participants and the responsible physician independently from study procedures. Patients will be informed that study participation is voluntary, that they may withdraw from the study at any time and that withdrawal of consent will not affect their subsequent medical assistance and treatment. Patients will be given at least a day to consider participation in the study. Study procedures comprises of assessments with questionnaires and structured interviews at baseline, 4, 52, 104, 156 weeks, and of a duration around one hour each. These are described below and in Table 1.

**Table 1 Tab1:** Study assessments

*Study periods*	*Assessment 1 (Baseline)*	*Assessment 2*	*Assessments 3, 4 and 5*
*Time (weeks)*	*0*	*4*	*52, 104, 156*
*Inclusion/Exclusion Criteria*	*X*		
*Written Informed Consent*	*X*		
*Patient characteristics*	*X*		
*Medical History*	*X*		
*Retention*^*a*^	*X*	*X*	*X*
*Opioid agonist prescription*^*a*^	*X*	*X*	*X*
*Treatment adherence*^*a*^	*X*	*X*	*X*
*Frequency of visits*^*a*^	*X*	*X*	*X*
*Treatment Outcomes Profile (TOP)*^*b*^	*X*	*X*	*X*
*Health section of Opiate Treatment Index (OTI)*^*b*^*, including nose-related problems*	*X*	*X*	*X*
*Symptom-Checklist 27 (SCL-27)*^*b*^	*X*	*X*	*X*
*Adverse Events*^*b*^	*X*	*X*	*X*
*Opioid Agonist Scale*^*1,c*^	*X*	*X*	
*VAS Subjective effects*^*2,c*^	*X*	*X*	
*VAS Craving*^*c*^	*X*	*X*	*X*
*VAS Satisfaction*^*c*^	*X*	*X*	*X*

^1^20–30 min after DAM application

^2^10 min after DAM application

^a^Used to assess feasibility of IN DAM

^b^Used to assess safety of IN DAM

^c^Used to assess acceptability of IN DAM

Patients will remain in the study if they change route of administration of DAM and will continue assessments even if they no longer receive IN DAM until study completion after three years. Patients who switch from IN DAM to another DAM route of administration and subsequently switch back to IN DAM will be allowed to do so, as it is an observational study of clinical procedures. Short-term switches to other forms of DAM or OAT due to external circumstances such as vacations abroad (where DAM cannot be taken), illness, hospitalisations or similar will be considered as continuous IN treatment, as the basic prescription will not change. If a patient switches to another route of DAM administration as per prescription, this will be systematically assessed, and a change back to IN DAM as well.

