### Primary outcome assessment

The primary outcome is retention in treatment with IN DAM after 4 weeks, 52 weeks, 104 weeks and 156 weeks. Success on primary outcome is defined as participants receiving IN DAM at each follow-up. Therefore, we will assess the prescription at the time point of assessment, and patients receiving IN DAM at the time point of assessment will be considered retained. However, since patient may switch to another route of DAM administration and then switch back to IN DAM within the follow-up periods, we will also separately calculate continuous IN DAM retention from “intermittent” IN DAM retention for patients changing and returning to and from other routes of DAM, and will assess time spent in prescription of IN DAM compared to other routes of administration.

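### Leaving HAT ends all data collection, so week 52 to 156 secondary and safety results describe patients still in HAT, and participants who re-enter are left unclassified for retention

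*Protocol article*

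**What the plan says.** All references are to the protocol article.

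- **Discontinuation**, on who is withdrawn: "Participants will be withdrawn from the study if they withdraw informed consent or if they leave HAT".
- **Discontinuation**, on what follows: "There will be no final examinations related to the study", and "Dropouts will be recorded as this relates to primary outcome (retention in treatment), but not followed up". Reasons for dropout are to be assessed. Earlier data are kept: "If a patient withdraws, only anonymised data gathered until this time point will be used".
- **Study procedures**, on patients who change route: they "will continue assessments even if they no longer receive IN DAM until study completion after three years". Discontinuation repeats this for anyone who remains in DAM treatment and does not withdraw consent. Short interruptions for travel, illness or hospital stays count as continuous intranasal treatment.
- **Primary outcome assessment**: "patients receiving IN DAM at the time point of assessment will be considered retained". Continuous and intermittent retention are to be separated "for patients changing and returning to and from other routes of DAM". Leaving HAT and coming back is not mentioned.
- **Study objectives and hypotheses**: besides retention, the study expects intranasal DAM to be safe, prescribed injections to fall and illicit opioid use to decline.
- **Safety**: adverse events are monitored for the duration of the study, which for a leaver ends at withdrawal.

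**The concern.** This is a data-collection rule. An analysis plan can model missing values, but it cannot recover observations that the protocol says will not be made.

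The loss is plausibly informative. The Introduction says that limited response to oral DAM "may lead to treatment drop-out, ongoing illicit substance use, diversion of DAM tablets and delinquency". It lists drop-out and illicit use side by side as consequences of the same cause. It does not say that leavers use more than stayers, but a shared cause makes that a reasonable inference.

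The rule is also uneven. The plan follows people after they stop the study route, yet stops at exit from HAT, where follow-up would be most informative. On a plain reading, that exit includes transfer to conventional agonist treatment. The limitations section does not mention this loss.

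Two things are at stake. A decline in illicit use or injecting between baseline and weeks 52 to 156 could partly reflect who remains under observation. And the primary count could depend on whether the withdrawal rule or the point-in-time rule is applied to a participant who re-enters HAT.

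**Working it through.** The document states no exit rate and no illicit-use rate, so there is no figure to reproduce.

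**Inputs from the document:** the rules above; visits at weeks 0, 4, 52, 104 and 156; 100 to 200 participants expected.

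**Inputs assumed:** share leaving HAT by week 156, d = 20-40%; illicit opioid use at week 156 in stayers, S = 30%, and in leavers, L = 50-70%; baseline use 45%.

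**1. Who is observed.** With d = 20-40%, 80 to 60 of 100, or 160 to 120 of 200, could still be assessed at week 156. With no final examination, a leaver's last assessment can be up to 52 - 4 = 48 weeks old at exit in the first year, and up to 52 weeks old later.

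**2. Size of the error.** Whole-cohort use is (1-d)·S + d·L. Stayers alone show S. Set against the baseline of all enrolled, the decline is overstated by d·(L-S).

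| d | L | Whole-cohort use | d·(L-S) | Apparent fall from 45% | Whole-cohort fall |
|---|---|---|---|---|---|
| 20% | 50% | 24 + 10 = 34% | 4 points | 15 points | 11 points |
| 30% | 60% | 21 + 18 = 39% | 9 points | 15 points | 6 points |
| 40% | 70% | 18 + 28 = 46% | 16 points | 15 points | -1 point (a rise) |

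A comparison within the same persons changes the expression but does not remove the problem. The error becomes d × (decline in stayers - decline in leavers), which equals d·(L-S) when both groups start from the same baseline.

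**3. Direction.** If L = S, the error is zero. If leavers do better, for example L = 20% and S = 40% with d = 10-40%, it is -2 to -8 points, so the decline is understated.

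**4. What can be said without assuming L.** Whole-cohort use lies between (1-d)·S (no leaver uses) and (1-d)·S + d (all leavers use). With S = 30% this gives 24-44% at d = 20%, 21-51% at d = 30% and 18-58% at d = 40%. The width equals d.

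**5. Retention.** A leaver is not receiving intranasal DAM and counts as not retained under both sections. If a share r of leavers is back on intranasal DAM at the visit but already withdrawn, retention is understated by d·r. With r assumed at 10-50%, that runs from 20% × 10% = 2 points to 40% × 50% = 20 points. The document gives no basis for r.

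**The case against.** A reader might infer that every hypothesised improvement is biased upward. The document does not support this. Retention is the first hypothesis, and dropouts are recorded for it as failures. For the other outcomes, the error takes the sign of the difference between leavers and stayers. Exits through abstinence or transfer to other stable care could reverse it, and prescribed injections within HAT stop at exit anyway.

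A reader might also infer that the withdrawal rule contradicts the point-in-time retention rule. It does not do so for a patient who has simply left. The provision on switching and returning concerns DAM routes within treatment, and short interruptions are covered separately. What remains is an unaddressed case of unknown frequency.

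Three further objections have weight:

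- Data up to withdrawal are used, and reasons for dropout are already collected.
- The Data analysis section names linear mixed models for repeated measures alongside Fisher and Wilcoxon-Mann-Whitney tests, so comparing stayers with everyone's baseline is not the only stated analysis. A mixed model uses leavers' earlier data, but it does not cure dropout that depends on unobserved later use, and those earlier data may be nearly a year old.
- Serious events are limited to those where attribution to intranasal administration or to data collection cannot be excluded. Many late deaths after exit would fall outside that definition, which narrows the safety part of the concern without removing it.

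Handling of missing data may also be set out in an analysis plan not shown here. That defence does not reach a rule that stops collection.

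**Conclusion.** The point holds in limited form. Leaving HAT makes later secondary and safety data missing by design, plausibly not at random, so the week 52, 104 and 156 findings on illicit use, risk behaviour and adverse events apply to patients still in HAT. The likely direction favours intranasal DAM, by about 4 to 16 points under the assumed rates. Those rates place leavers above stayers throughout; with equal rates the error vanishes, and with benign exits it changes sign. The primary retention result is not inflated. It may be understated, because a participant who re-enters meets the point-in-time rule but has already been withdrawn; the amount cannot be judged from the document. The change is worth making but does not undermine the primary outcome.

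**What to change.** 1. Amend Discontinuation so that leaving HAT without withdrawing consent does not end study participation. A participant who re-enters a study centre within 156 weeks resumes assessments, is classified by the point-in-time rule in Primary outcome assessment, and counts as intermittent, not continuous, retention.
2. In addition to the reason already recorded, take the exit date and last known vital status from the chart.
3. For binary secondary outcomes, report the within-person available-case result together with bounds over all enrolled, counting leavers first as all improved and then as none improved. Show planned exits and transfers separately. A single composite that counts every exit as failure should appear only as one end of this range, since alone it builds in the opposite bias.
4. Limit the conclusion from the available-case result to patients still in HAT, and add this loss to the limitations.

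These changes concern study participation and reporting only, not treatment. The cost is a short amendment, one or two chart fields, and wider, less favourable secondary figures.

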### Data analysis

Statistical analysis of retention in treatment will be conducted with the appropriate statistical methods, depending on measurement-level of the variables (binary: t-test for repeated measures; interval: survival analysis).

The secondary outcomes will be assessed using Fisher’s exact, Wilcoxon–Mann Whitney, and interaction terms from Linear Mixed Models for binary, interval, and repeated measures, respectively.

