## Methods

### Study design

The study is designed as an exploratory prospective multicentre clinical cohort study. Every HAT centre in Switzerland was invited to participate and 18 confirmed their participation. Given that there are 23 specialist outpatient centres offering HAT in Switzerland, this study is representative of the treatment system [29]. Within this treatment system, these outpatient centres provide HAT to around 1600 patients, which has been relatively constant within the last two decades [30]. Enrolled participants will switch from oral or injectable DAM (treatment as usual arm) to intranasal DAM. Follow-up will occur over three years, with assessments at baseline (t0), and after 4 (t4), 52 (t52), 104 (t104) and 156 (t156) weeks. These timepoints are standard follow-up periods when measuring retention in OAT [31]. Specifically, the first 4 weeks in OAT are particularly important as the risk of mortality is elevated when compared with the remainder of time receiving OAT [32]. Long-term retention in HAT has also been studied at similar time points (e.g., 2 years in Germany, 2 years in Spain, 4 years in the Netherlands) [33–35].

Participants in n-HAT will receive Diaphin^®^ IV 100 mg/ml (DiaMo Narcotics, Thun), approved in Switzerland for IV treatment of OUD in the HAT setting. It will be administered into the nostrils with a mucosal atomisation device (Fig. 1). Atomisers are personalised, disinfected following each administration and replaced every 7 days. Just like conventional treatment with IV and IM DAM, long-acting oral opioids such as methadone or and slow-release oral morphine can be used as additional medication in order to prevent withdrawal. Participants will also be allowed to combine nasal with oral, IV and IM DAM. The dosing of IN DAM and of DAM through other routes of administration will remain an individual decision of patients and prescriber. Therefore, patients will not receive the same dosification, but rather receive an IN DAM dosification that align with their needs. There is no limitation on concomitant opioid and/or non-opioid medication to be prescribed. This study design is meant to be as comparable to the current Swiss HAT setting as possible.

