### Study objectives and hypotheses

The study aims at investigating whether IN DAM is clinically feasible, acceptable to patients, and safe to use in HAT. The primary outcome measure (POM) is retention in HAT with the IN DAM route of administration after 4 weeks, 52 weeks, 104 weeks and 156 weeks. The secondary outcome measures (SOM) are prescriptions and routes of administration of other opioid agonists, illicit substance use, risk behaviours, delinquency, health and social functioning, treatment adherence, craving for opioids and other substances, satisfaction with prescribed opioid, subjective effects, quality of life, physical health, and mental health.

We hypothesise that patients receiving IN DAM in HAT will be retained in treatment with this route of administration over short and long time periods. Furthermore, patients are expected to report high satisfaction within IN DAM. Thirdly, we hypothesise IN DAM to be safe, the number of prescribed injection events to decrease and use of illicit opioids to decline.

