### Sample size and power calculation

We aim to include all patients willing to participate in the study. As this is an exploratory observational study, it is not possible at this point to exactly predetermine the final sample size, as it depends on the number of patients interested in and qualifying for n-HAT and consenting to participation in this clinical observation. We think that over the planned accrual time of two years, it is realistic to include between 100 and 200 participants who will try out IN DAM.

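### The repeated-measures t-test named for yes/no retention tests change between occasions, not whether patients are retained on intranasal DAM

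*Protocol article*

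**What the plan says.** All references are to the protocol article.

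- **Outcome.** Primary outcome assessment sets the time points: "The primary outcome is retention in treatment with IN DAM after 4 weeks, 52 weeks, 104 weeks and 156 weeks". It also sets the scale: "patients receiving IN DAM at the time point of assessment will be considered retained". Each patient is therefore a yes or a no at each visit. The same section plans separate results for continuous and intermittent retention, and for time spent on intranasal (IN) DAM.
- **Hypothesis.** Study objectives and hypotheses: "We hypothesise that patients receiving IN DAM in HAT will be retained in treatment with this route of administration over short and long time periods". No reference rate or margin is attached.
- **Test.** Data analysis chooses the method "depending on measurement-level of the variables (binary: t-test for repeated measures; interval: survival analysis"). It does not say which occasions the t-test compares, and it gives no significance level.
- **Start of observation.** Under Study procedures, enrolment comes after the choice of route: "Participants will be recruited only after the decision for nasal DAM is made by the participants and the responsible physician independently from study procedures". Table 1 in that section marks retention at week 0 as well as at every follow-up. Study design says: "Enrolled participants will switch from oral or injectable DAM (treatment as usual arm) to intranasal DAM".
- **Size.** Sample size and power calculation: "it is realistic to include between 100 and 200 participants who will try out IN DAM". This is an accrual forecast. No power calculation is given.

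**The concern.** A t-test for repeated measures compares the mean of a continuous variable on two occasions in the same people. Here the variable is 0 or 1, so its mean is the proportion on IN DAM, and the null hypothesis is that this proportion did not change. The study asks something else: whether the proportion is high enough, for long enough, to call the route feasible.

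The binary status is the article's own success criterion at all four time points. If it is analysed as named, the p-value attached to it does not bear on the hypothesis. A good result could be reported as a significant fall, or a poor one as a significant rise, depending on what week 0 means.

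**Working it through.** The article gives no power, alpha or effect size, so there is no figure of its own to reproduce. The check is what the named test would report under each comparison the text allows.

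**Inputs.** n = 100, 150 and 200, spanning the forecast in Sample size and power calculation. Follow-up retention of 90%: the Discussion describes preliminary four-week retention of over 90% as positive, and 90% is used as a round figure. Two-sided alpha of 0.05 is assumed.

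**Reading A: against week 0, start value 100%** (IN DAM already begun; inferred, not printed). Each difference is 0 or −1. With a proportion p retained,

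t = −(1−p) / √[p(1−p)/(n−1)] = −√[(n−1)(1−p)/p].

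| n | lost | t | p, paired t | p, exact McNemar (2 × 0.5^lost) |
|---|---|---|---|---|
| 100 | 10 | −√(99/9) = −3.32 | 0.0013 | 0.002 |
| 150 | 15 | −√(149/9) = −4.07 | 0.00008 | 0.00006 |
| 200 | 20 | −√(199/9) = −4.70 | 0.000005 | 0.000002 |

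The statistic can never be positive, so the only possible results are no detected change or a fall. Four losses are enough for p=0.045 at each of the three sizes; at n=200 that is 196/200 = 98% retained. Exact McNemar for four losses gives 2 × 0.5⁴ = 0.125, so the t approximation matters near 100%. At 90% the two tests agree, and the result there comes from the null hypothesis and not from the t distribution.

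**Reading B: against week 0, start value 0%** (baseline before the switch, which Study design permits). By symmetry, only 10% on IN DAM at follow-up gives t=+3.32, p=0.0013 at n=100. Very poor retention would appear as a significant gain.

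**Reading C: follow-up against follow-up.** Neither value is fixed by enrolment, so the test is not degenerate. With 90% at week 4, 80% at week 52 and no returns, n=100 again has 10 changes in one direction and p=0.0013. This measures change only: 90% at both visits and 50% at both visits each give a mean difference of 0 (0.90−0.90 and 0.50−0.50).

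**What answers the question.** The proportion retained with an exact 95% interval. At 90% observed:

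- n=100: 82.4% to 95.1%
- n=150: 84.0% to 94.3%
- n=200: 85.0% to 93.8%

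**The case against.** The other side has several sound points.

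- **The comparison is not stated.** A reader might infer that the plan tests each follow-up against a 100% baseline and would therefore declare failure at 90%. The article does not say so. The primary outcome is defined only at the follow-ups, Table 1 does not say how the week-0 entry is used, and Study design allows a baseline before the switch. Rejecting no change would also not refute a hypothesis that has no benchmark. The figures under Readings A and B are therefore conditional.
- **The t-test itself does limited numerical harm.** At 90% retention McNemar leads to the same conclusion. This stands, and it means that swapping one paired test for another would not cure the problem.
- **Survival analysis is also named.** A reader might conclude that the whole primary analysis misses the study question. It does not: time on IN DAM suits a hypothesis about short and long retention, and that part is sound.
- **Dropout handling.** A reader might suspect that leaving HAT would be treated as ordinary censoring. No such rule is stated, and Discontinuation points the other way: "Dropouts will be recorded as this relates to primary outcome (retention in treatment), but not followed up". Censoring rules may properly be left to the analysis plan.
- **The study is exploratory and the article is condensed.** True, but the method is named outright, so this is not a detail left to a fuller document.

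None of this rescues the t-test, because no reading of it tests whether patients are retained.

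**Conclusion.** The point holds for the binary analysis of the primary outcome and goes no further. In a single cohort without comparator or benchmark, the named test detects change between occasions and cannot support the stated hypothesis. Against baseline it is uninformative, because the start value is a constant fixed by enrolment whichever way week 0 is read. Between follow-ups it is a test of change, made with a method meant for continuous data.

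The p-values rest on three assumptions: comparison with week 0, a start of 100% (or 0%), and two-sided alpha of 0.05. The conclusion that the test misses the hypothesis needs none of them. Because survival analysis is also planned and the study is exploratory, this is a should-fix.

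**What to change.** In Data analysis, replace the t-test for the binary form with the following:

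1. **Primary.** The proportion receiving IN DAM at weeks 4, 52, 104 and 156 among all enrolled, counting recorded dropouts from HAT as not retained, with Wilson or exact 95% confidence intervals. If a test is wanted, set a benchmark rate beforehand.
2. **Secondary description, if change between follow-ups is of interest.** A paired binary method: McNemar, Cochran's Q or a logistic repeated-measures model.
3. **Survival analysis.** Keep it for time to the end of continuous IN DAM retention. Report it separately from the point-in-time status, under which Primary outcome assessment lets a patient who switched away and returned count as retained.

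The cost is wording only. No new data are needed.

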### Secondary outcome assessment

Opioid agonist prescriptions including substance, galenics, dose and route of administration in the past 4 weeks will be assessed using patient’s the medical charts at each time point (t0, t4, t52, t104, t156).

Adherence to treatment and frequency of visits in the past 4 weeks will be assessed using the recorded scheduled and realised dispensings in the patient’s medical charts at each time point (t0, t4, t52, t104, t156).

Illicit substance use, delinquency, health and social functioning and quality of life will be assessed by the Treatment Outcome Profile (TOP) at each time point (t0, t4, t52, t104, t156). The TOP is a 20-item instrument which assesses substance use, injecting risk behaviour, and crime by self-report in the past 4 weeks [38]. Quality of life and social functioning will be assessed using the proposed 0-to-20-point scale of the TOP at each time point (t0, t4, t52, t104, t156).

Opioid craving in the past 7 days will be measured by visual analogue scales (VAS) at each time point (t0, t4, t52, t104, t156). Craving for alcohol, benzodiazepines and cocaine will be measured likewise. Acceptability of nasal DAM will be assessed by VAS on satisfaction with the different routes of administrations in DAM. Additionally, questions on the willingness to continue with the current prescription will be asked.

Subjective DAM effects will be measured by visual analogue scales (VAS) twice (t0 and t4), 10 min after DAM application. The VAS presents the participant a rating scale which represents the spectrum of “opioid high”, heroin-typical effects, good effects, bad effects, pleasure and feeling unwell: the left end indicates “none” while the right end indicates “extreme” effects.

Furthermore, subjective effects of opioids will be assessed using the self-reported German version of the Opioid Agonist Scale at baseline and 4 week follow-up point (t0 and t4) [39]. Between 20 and 30 min after DAM administration, participants will rate the extent to which they experienced each of 16 morphine-like symptoms on a five-point scale from “not at all” to “extremely”.

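### The tests named for the secondary outcomes do not test the before-after changes that the study hypothesises in its single cohort

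*Protocol article*

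**What the plan says.** The Data analysis section of the protocol article gives one sentence to the secondary outcomes. They will be "assessed using Fisher’s exact, Wilcoxon–Mann Whitney, and interaction terms from Linear Mixed Models", assigned to binary, interval and repeated measures in that order. It names no groups to be compared and no factor for the interaction.

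The Study design section describes the study as "designed as an exploratory prospective multicentre clinical cohort study", "with assessments at baseline (t0), and after 4 (t4), 52 (t52), 104 (t104) and 156 (t156) weeks". It also states: "Enrolled participants will switch from oral or injectable DAM (treatment as usual arm) to intranasal DAM". Under Study procedures, "Participants will be recruited only after the decision for nasal DAM is made by the participants and the responsible physician", so nobody is enrolled who has not already chosen the intranasal route.

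Under Study objectives and hypotheses, the authors expect "the number of prescribed injection events to decrease and use of illicit opioids to decline". They also hypothesise retention, high satisfaction and safety, and none of these is worded as a change from baseline.

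Table 1 and the Secondary outcome assessment section show repeated collection throughout. For example, "quality of life will be assessed by the Treatment Outcome Profile (TOP) at each time point (t0, t4, t52, t104, t156"). The subjective-effects scales are taken at t0 and t4 only; the other secondary measures are taken at all five visits.

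**The concern.** The named tests answer questions between groups, while the design and two of the hypotheses pose a question within one group. Someone following the Data analysis section literally has two options for asking whether illicit use or injecting fell after the switch. One is to apply Fisher or Mann-Whitney to the same people at two visits, which ignores the pairing. The other is to look for an interaction term that, even with a factor supplied, estimates a different quantity.

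The study could then fail to detect declines that did occur. The same insensitivity matters for safety. Nasal symptoms are a safety measure here and safety is a hypothesis, so a test that is slow to detect worsening favours the expected conclusion.

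**Working it through.** **Step 1. Match each test to what it needs and to what the article supplies.**

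| Stated method | What it needs | What the article supplies |
|---|---|---|
| Fisher's exact (binary) | Two independent groups | One cohort; no groups named |
| Wilcoxon-Mann-Whitney (interval) | Two independent groups | One cohort; no groups named |
| Interaction in a linear mixed model (repeated measures) | A second factor besides visit | No factor named |

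The treatment-as-usual label in Study design refers to the participants' own treatment before the switch. It is not a group followed alongside.

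**Step 2. What an interaction would estimate.** Write the mean at visit *t* in subgroup *g* as μ(g,t) = α + β(t) + γ(g) + δ(g,t). In a single cohort without subgroups, the change from baseline is β(t) − β(0), the visit effect. The interaction δ says only whether that change differs between subgroups. If two subgroups improve equally, δ is zero although the hypothesis of a decline is true.

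**Step 3. What happens if the two tests are used on paired visits.** The article states no alpha, effect size or power, so there is no figure to reproduce. The only input from the document is the expected enrolment of 100 to 200 (Sample size and power calculation), treated here as complete pairs. Correlation, effect size and a two-sided 5% level are assumptions.

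For a mean difference between visits, an independent-groups test uses variance 2σ²/n, but the true variance is 2σ²(1 − ρ)/n. The standardised statistic therefore has standard deviation √(1 − ρ), and the actual size is 2[1 − Φ(1.96/√(1 − ρ))]:

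- ρ = 0: 1.96/1 = 1.96, size 5.0%
- ρ = 0.3: 1.96/0.837 = 2.34, size 1.9%
- ρ = 0.5: 1.96/0.707 = 2.77, size 0.56%
- ρ = 0.7: 1.96/0.548 = 3.58, size 0.03%

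Simulation of bivariate normal pairs agrees with this approximation. The binary outcome is a cut of the same latent variable, so ρ is the latent correlation. Alternatives: a binary fall from 50% to 38%, and a shift of 0.25 SD. There were 6,000 runs for binary and 3,000 for interval outcomes. Results for n = 150:

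| ρ | Size: Fisher / McNemar | Size: Mann-Whitney / signed-rank | Power: Fisher / McNemar | Power: Mann-Whitney / signed-rank |
|---|---|---|---|---|
| 0 | 0.042 / 0.037 | 0.052 / 0.050 | 0.52 / 0.50 | 0.56 / 0.56 |
| 0.3 | 0.021 / 0.036 | 0.022 / 0.050 | 0.53 / 0.60 | 0.58 / 0.72 |
| 0.5 | 0.014 / 0.036 | 0.007 / 0.056 | 0.53 / 0.68 | 0.58 / 0.85 |
| 0.7 | 0.005 / 0.035 | 0.000 / 0.046 | 0.54 / 0.79 | 0.59 / 0.97 |

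Over n = 100, 150 and 200 and ρ from 0.3 to 0.7, Fisher's actual size is 0.003 to 0.021 and Mann-Whitney's 0.000 to 0.022. A separate rerun gave upper ends of 2.5% and 2.3%. The power given up is 7 to 27 points for Fisher (smallest 0.597 − 0.529 at n = 150, ρ = 0.3; largest 0.570 − 0.305 at n = 100, ρ = 0.7). For Mann-Whitney it is 10 to 53 points (0.842 − 0.739 at n = 200, ρ = 0.3; 0.880 − 0.349 at n = 100, ρ = 0.7). At ρ = 0 the independent and paired tests agree closely, so the neglected pairing is the cause.

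**Step 4. A safety illustration.** Assume that a nasal symptom rises from 20% to 30%, with n = 150 and ρ = 0.7. Two simulation runs put Fisher's power at 43% and 46%, and exact McNemar's at 71% and 72%.

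**The case against.** The strongest reply is that the sentence gives repeated measures to a linear mixed model, and nowhere says that Fisher or Mann-Whitney will compare the same people at two visits. Groups do exist within the cohort: previous oral or injectable DAM, continuous or intermittent intranasal retention, and patients who leave the intranasal route but keep their visits. Fisher and Mann-Whitney are valid between such groups, and a visit-by-group interaction can be estimated. Naming the factor could be a detail for the full protocol or analysis plan. The study is also exploratory, and these are secondary outcomes.

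Much of this stands. A reader might infer that the tests are invalid for every secondary outcome, that the interaction can have no meaning, or that the plan has committed to an unpaired analysis of paired data. The article supports none of these. It names no comparison, some hypotheses are not about change, and a subgroup factor could be supplied. Step 3 therefore shows the cost of one possible use, not of a stated one.

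The reply does not rescue the two decline hypotheses. Even with previous route as the factor, the interaction would test whether change differs by route, not whether injecting or illicit use fell. Nor does the split into binary, interval and repeated measures help, because every secondary measure in Table 1 is taken at two or more visits. This is a mismatch between what the article states and the design it states, rather than an omitted detail.

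**Conclusion.** The point holds in this form: none of the methods named for the secondary outcomes is, as written, a correct test of the two hypothesised declines. The mixed model is a suitable tool; the choice of the interaction as the quantity to report is what does not fit.

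If Fisher or Mann-Whitney were used on baseline versus follow-up, the actual size would be about 0 to 2.5% instead of 5%, with power losses from 7 to 53 points depending on test, n and correlation. These figures rest on assumed correlations of 0.3 to 0.7, assumed effects and an assumed alpha. A reader might infer inflated false positives from the word invalid. With positive within-person correlation the error runs the other way, so the risk is missed change, including missed harm, and not a false claim of benefit.

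Severity is moderate: the outcomes are secondary, the study is exploratory, and the sentence does not touch the primary outcome.

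**What to change.** Reword the Data analysis section:

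- For change from t0, report the visit effect (t4, t52, t104 and t156, each versus t0) from a mixed model with a participant random effect. Use a linear model for scales, and a logistic mixed model or GEE for binary outcomes.
- For a comparison of one follow-up visit with t0, McNemar (binary) and Wilcoxon signed-rank (interval) are adequate.
- Keep Fisher, Mann-Whitney and interaction terms only for between-participant subgroups that are named, for example previous oral versus previous injectable DAM.
- In Study design, replace the treatment-as-usual arm label with own previous treatment.

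The cost is wording only, with no new data or visits. The Discussion already cites four-week retention findings, so the change should be made before the secondary outcomes are analysed.
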